# Study protocol on effectiveness of yoga practice on composite biomarker age predictors (yBioAge) in an elderly Indian cohort- two-armed open label randomized controlled trial

**DOI:** 10.1186/s12877-023-04517-6

**Published:** 2023-12-15

**Keywords:** Biological age, Yoga, Aging

## Abstract

**Introduction:**

The recent development of robust indices to quantify biological aging, along with the dynamic epidemiological transitions of population aging generate the unmet need to examine the extent up to which potential interventions can delay, halt or temporarily modulate aging trajectories.

**Methods and analysis:**

The study is a two-armed, open label randomised controlled trial. We aim to recruit 166 subjects, aged 60–75 years from the residential communities and old age clubs in Bangalore city, India, who will undergo randomisation into intervention or control arms (1:1). Intervention will include yoga sessions tailored for the older adults, 1 h per day for 5 days a week, spread for 12 months. Data would be collected at the baseline, 26^th^ week and 52^nd^ week. The primary outcome of the study is estimation in biological age with yoga practice. The secondary outcomes will include cardinal mechanistic indicators of aging- telomere length, interleukin-6 (IL-6), tumor necrosis factor receptor II (TNF-RII), high sensitivity c-reactive protein (hsCRP)], insulin signaling [insulin and IGF1], renal function [cystatin], senescence [growth differentiating factor 15 (GDF-15)] and cardiovascular function [N-terminal B-type natriuretic peptides (NT-proBNP)]**.** Analyses will be by intention-to-treat model.

**Ethics & dissemination:**

The study is approved by the Institutional Ethics Committee of Swami Vivekananda Yoga Anusandhana Samsthana University, Bangalore (ID:RES/IEC-SVYASA/242/2022). Written informed consent will be obtained from each participant prior to inclusion.

**Trial registration number:**

CTRI/2022/07/044442.

## Introduction 

Global ageing, paralleled with increasing mental, behavioural and cardiovascular health morbidities, elicits many public health concerns. This demographic transition has been estimated to lead to a worldwide increase in the prevalence of older adults aged ≥ 60 years by 500 million over 15 years [from 900 million in 2015 to 1400 million by 2030] [1, 2]. In India, older adults constitute 8.6% of the total population as per Census 2011, projected to reach 19% by 2050 [3]. Unfortunately, the increase in lifespan has not been paralleled with an equivalent increase in healthy life expectancy or health span [4, 5]. Hence, developing and implementing anti-ageing therapies or interventions that could "healthy" life span has received significant scientific attention [5, 6]. The pre-clinical experimental evidence supports the feasibility of interventions for extending healthy life span in model organisms. However, in humans, the lengthy lifespan and the delayed time course for the symptomatic manifestation of ageing-related health decline pose barriers to clinical translation. To this end, a quest has been to develop robust markers or indices that could quantify the process of biological ageing, termed as the "BA estimates" [6]. Based on the complexity of the ageing process in humans, reliance on a single-point measurement has been considered a limitation [4, 5]. Though several biomarkers mimic age-related physiological deregulation at individual levels, composite predictors derived from merging multiple biomarkers into single latent variables has been considered a better approach to capture the complex aetiology of the ageing process. Developing these quantifiable indices of ageing is considered as the most critical milestone of geriatric research to aid in the longitudinal tracking of the trajectory of physiological decline. Klemera and Doubal-based Biological Age (KDM-BA) is such an algorithm-based measure that represents the status of integrity of multiple organ systems in the body [7]. KDM-BA is derived from a panel of various biomarkers measuring system integrity, including cardiovascular, renal, hepatic, immune, and metabolic function: albumin, blood urea nitrogen, creatinine, C-reactive protein, cytomegalovirus optical density, glycated haemoglobin total cholesterol, white blood cell count, lymphocyte per cent, mean corpuscular volume, systolic blood pressure, low-density lipoprotein- cholesterol. Based on the National Health Insurance Service-National Sample Cohort (NHIS-NSC) database, KDM-BA predicts morbidity, mortality, indicators of health span and age-related disease incidence in different populations as reported [7].

Several promising strategies have been posited as potential geriatric interventions in humans for their effects on health span. Lifestyle interventions (physical activity, calorie restriction, etc.) have restored immune functioning in aged individuals [8–12]. Dietary interventions included periodic fasting mimicking diets, protein restriction, drugs that inhibit the growth hormone/IGF-I axis, the mTOR–S6K pathway, or AMPK/sirtuins-based drug targets [13]. To this end, a recently reported secondary analysis of the landmark clinical trial “CALERIE” [14] indicates the potential of lifestyle interventions like calorie restriction in harnessing the process of biological ageing in humans with favourable changes in biomarkers related to cardiovascular and glucoregulatory functions. Yoga is a mind–body lifestyle modification technique, an amalgamation of physical activity, meditation and breathing techniques. A broad spectrum of health benefits for older adults has been reported to be associated with yoga [15–23]. However, most of the reported studies on yoga have targeted mobility, flexibility, cognition, gait, frailty, self-rated health and well-being as the outcomes [24–27]. Several preliminary reports also support the anti-ageing effects of yoga via key hallmarks of biological ageing such as telomere, attrition, regulation of inflammation and genome instability via DNA damage [28, 29].

There have been mechanistic postulates as well supported by molecular evidence base to support these beneficial aspects of yoga as an intervention, particularly for organ-specific or cellular functions. These insights could form an overarching framework for the exploration of the cumulative benefits of yoga in aiding physiological integrity. Hence, we aim to test the effectiveness of yoga in improving the multisystem decline in physiologic markers using KDM-based BA estimates.

Though the predictability of physiological status is well established through KDM-based age predictors, these predictors do not include several cardinal mechanistic biomarkers underlying the ageing process. Hence, we also propose to include a secondary list of blood-based biomarkers adapted from the study “Targeting Aging with Metformin (TAME) [5]. The TAME study includes a panel of outcome variables proposed to be used for geriatric intervention trials targeting healthy lifespan [5], including cardinal markers like telomere length, inflammation [interleukin-6 (IL-6), tumour necrosis factor receptor II (TNF RII), high sensitivity c-reactive protein (hs-CRP)], insulin signalling [insulin and IGF1], renal function [cystatin], senescence [growth differentiating factor 15 (GDF-15)] and cardiovascular function [N-terminal B-type natriuretic peptides (NT-proBNP)].

**Fig. 1 Fig1:**
[figure not shown]
Trial profile

### Randomisation and blinding

An external statistician will generate a randomization list using a sequence randomizer. The list will be transferred into separate sealed envelopes and opened by research assistants and the participant immediately following the baseline assessment. As complete blinding is not possible due to the nature of the intervention to reduce the detection bias, investigators involved in evaluating outcome measures would be blinded for the randomization groups.

### Intervention

Participants randomized to the yoga group will receive a yoga module that has been tested for efficacy, safety and feasibility for older individuals [31]. The module effectively improves the quality of life and sleep in elderly individuals [32] and will comprise of a combination of yoga postures, breathing practices, meditative techniques, and relaxation. The physical postures will consist of loosening and stretching exercises followed by practice of physical postures (a*sana)* in standing, sitting, prone, and supine positions followed by *pranayama*. It provides a moderate intensity of physical activity. The patients will be instructed to follow a specific breathing pattern, culminating in a relaxation response during the practice. The practices will be interspersed by relaxation techniques to avoid any strain or exhaustion to the participants. Certified yoga instructors experienced in teaching older adults will deliver yoga classes in groups. The 60-min classes will be offered at multiple locations 5 days a week. The groups would comprise 20–25 participants, adequate to provide individual attention to each participant. Overall, the yoga intervention will.

be divided into 2 phases: phase 1 including 120 supervised sessions at the centres; phase 2 including at-home yoga practice sessions for next 6 months (24 weeks) (Fig. 1).

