### Waitlist group

We decided on a waitlist design for the inactive control group because we deemed it ethically acceptable alternative to continuing to give the inactive older persons with the care they need beyond the trial. They will be told to carry on with their regular daily activities (without participating in scheduled, routine exercise) while being recruited. These participants will receive the same yoga-based lifestyle intervention offered to the intervention group following the completion of the 12 months study.

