## Statistical analyses

### Sample size

Total of 166 participants are planned to recruit for yBioAge which is estimated by g power software using a moderate effect size of f = 0.25 and a power of 80% (for alpha = 0.05), often recommended as appropriate power in behavioural research [41] the power analysis yielded a sample size of 128 participants. Allowing for 30% attrition in one year, we planned to recruit 38 participants per treatment condition to maximize power.

Baseline characteristics of participants will be summarised using mean and SD or median and IQR for continuous variables and frequency and percentage for categorical variables. The primary outcome analyses will observe intention-to-treat principle. Missing data will be replaced using Multivariate Imputation by Chained Equations in R studio software. Sensitivity analyses will be performed. Log binomial models will be estimated by generalised estimating equations. Mixed-effects linear regression models will be used. We will include outcomes at baseline, 26^th^ week and at the end of 52^nd^ week. All analyses will be performed in IBM SPSS, V.26 and in R (V.76). We will employ a statistical threshold of α = 0.05.

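### The sample size of 128 makes no allowance for clustering by yoga class in one arm, and the named mixed model states no class or instructor effect

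*Protocol article*

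**What the plan says.** The Intervention section of the protocol article describes group delivery: "Certified yoga instructors experienced in teaching older adults will deliver yoga classes in groups". It adds that "The 60-min classes will be offered at multiple locations 5 days a week" and gives the class size: "The groups would comprise 20–25 participants, adequate to provide individual attention to each participant". The programme has two parts, "phase 1 including 120 supervised sessions at the centres; phase 2 including at-home yoga practice sessions for next 6 months (24 weeks").

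The Waitlist group section leaves controls ungrouped: "They will be told to carry on with their regular daily activities (without participating in scheduled, routine exercise) while being recruited". According to the abstract, individuals are randomised 1:1.

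The Sample size section bases the calculation on software "using a moderate effect size of f = 0.25 and a power of 80% (for alpha = 0.05"). This gives 128 participants, raised to 166 for attrition. The section mentions no ICC, design effect or number of classes. The analysis paragraph that follows names mixed-effects linear regression with outcomes at baseline, week 26 and week 52. It does not state the random effects.

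**The concern.** This is a partially nested design. Participants are randomised individually, but only one arm is then taught in groups. Yoga participants share a class and an instructor for 120 supervised sessions, so their outcomes may be correlated. Controls have no corresponding grouping.

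If the correlation is positive, the yoga mean is less precise than its number of participants suggests. One of two things follows:

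- If the analysis models class, the test is better protected, but power falls below 80% because the sample size was set as if class did not matter.
- If the analysis omits class, the standard error is too small and the nominal 5% test rejects too often. A random effect for participant alone, which handles the repeated visits, does not absorb variation between classes.

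The number of classes is small, so even a modest ICC has a visible effect.

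**Working it through.** **Inputs from the protocol article.** f = 0.25, power 80%, alpha 0.05, N = 128 and 166 (Sample size); 1:1 allocation (abstract); classes of 20–25 (Intervention).

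**Assumptions.** Two-sided test; class membership is stable; classes are of equal size; ICC 0 to 0.05, because the documents give none.

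**Reproducing the plan's figure.** For two equal groups d = 2f = 0.5. The two-group test for independent participants needs a total of 127.5, so 128, or 64 per arm with power 80.1%. Adding 30% gives 128 × 1.30 = 166.4, which matches 166. The design effect in the stated sample size is therefore exactly 1.

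**Number of classes.** 166/2 = 83 in the yoga arm. 83/25 = 3.3 and 83/20 = 4.2, so about four. With 64 analysed per arm, that is m = 64/4 = 16 per class.

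**Formulas, with clustering in the yoga arm only.**

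- Design effect: DE = 1 + (m − 1) × ICC
- True variance of the difference relative to the naive variance: VR = (DE + 1)/2
- Type I error if class is ignored: 2 × [1 − Φ(1.96/√VR)]
- Power if class is allowed for: Φ(0.5/√((DE + 1)/64) − 1.96)

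**Results at 64 per arm, m = 16.**

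| ICC | DE | VR | Type I error, class ignored | Power, class allowed for |
|---|---|---|---|---|
| 0 | 1.00 | 1.000 | 5.0% | 81% |
| 0.01 | 1.15 | 1.075 | 5.9% | 78% |
| 0.02 | 1.30 | 1.150 | 6.8% | 75% |
| 0.05 | 1.75 | 1.375 | 9.5% | 67% |

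For ICC 0.05: DE = 1 + 15 × 0.05 = 1.75 and VR = 2.75/2 = 1.375. Then 1.96/√1.375 = 1.67, a two-sided error of 9.5%. For power, 0.5/√(2.75/64) = 2.41, and Φ(2.41 − 1.96) = 67%. Simulation with four classes and 40,000 replicates gave type I errors of 5.0%, 5.8%, 6.8% and 9.5%; other runs of the same set-up gave 9.3% to 9.5% at ICC 0.05.

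**If all 83 per arm are analysed, m = 20 to 25.** Type I error with class ignored is 6.1–6.4%, 7.2–7.8% and 10.7–12.1% at ICC 0.01, 0.02 and 0.05.

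**Small-sample degrees of freedom, 64 per arm.** The yoga mean has 4 − 1 = 3 df for its class-based variance and the control mean has 63. Satterthwaite df = (DE + 1)²/(DE²/3 + 1/63), which is 10.1, 9.1 and 7.3 at ICC 0.01, 0.02 and 0.05. Power from the noncentral t is then about 69%, 65% and 55%. At ICC 0 the same calculation gives 73%, so part of this loss comes from having only four classes.

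**Site.** A site effect shared by both arms acts differently. With balanced arms and site ICC 0.05, the site effect cancels from the difference and VR = 0.95. Then 1.96/√0.95 = 2.01, a type I error of about 4.4%. Ignoring site is slightly conservative.

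**The case against.** The strongest objection is that the article does not say the analysis treats participants as independent. It names a mixed model without its random effects, and a class or instructor term may be in the full protocol or statistical analysis plan, which are not shown. This stands. Silence on random effects in an article is not an error in itself. A reader might infer that the trial's error rate exceeds 5%, but the documents do not support that. Inflation needs both a positive ICC and an analysis that ignores class, and neither is established.

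Three further points have force:

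- The ICC may be low. The endpoint is a composite of mainly laboratory markers, read at week 52 after 24 weeks of practice at home. At ICC 0.01 the effect is small.
- The number of classes is derived, not stated, and the article does not say that membership is fixed. If participants move between classes, strict nesting is only an approximation.
- Location should not be counted as clustering in one arm. Individuals are randomised from several sites, so both arms can share a site. Only class and instructor effects are confined to yoga.

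None of this removes the planning point. The sample size is fixed in this article, and it omits a feature that the same article describes.

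**Conclusion.** The concern holds as a planning point with a conditional effect on the analysis. The 128 is an independent-participants figure, yoga is delivered in about four classes, and no class or instructor effect is stated.

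Over an assumed ICC of 0.01 to 0.05 at the protocol's own 64 per arm, power allowing for class is about 78% down to 67%, against the stated 80%. With small-sample degrees of freedom it is about 69% down to 55%. If class were ignored, type I error would be about 6% to 9%, or about 6% to 12% with all 83 per arm analysed. At ICC 0 the error rate is 5%.

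These figures start from 64 per arm, so that they show the effect of clustering alone. They rest on an assumed ICC, four equal classes and stable membership.

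**What to change.** - Record class and instructor for every yoga participant, including any change of class. Attendance is already to be logged (Adherence and attrition), so this adds little work.
- Prespecify in the primary mixed model a random class or instructor effect in the yoga arm only, with each waitlist participant as a singleton. Use Satterthwaite or Kenward–Roger degrees of freedom.
- Handle site separately, as a factor common to both arms.
- Restate power in the Sample size section over ICC 0 to 0.05, with the expected number of classes.

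The cost is a data field, a model term and a revised power statement. Enrolment need not rise if the lower power is stated openly. Holding 80% would take more participants: at ICC 0.05 with 20–25 analysed per class, about 93 to 101 per arm against 64. The downside is wider intervals, lower stated power and, with about four classes, an imprecisely estimated class variance.

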### Waitlist group

We decided on a waitlist design for the inactive control group because we deemed it ethically acceptable alternative to continuing to give the inactive older persons with the care they need beyond the trial. They will be told to carry on with their regular daily activities (without participating in scheduled, routine exercise) while being recruited. These participants will receive the same yoga-based lifestyle intervention offered to the intervention group following the completion of the 12 months study.

### Study outcomes

The primary outcome of the study is the change in scores of the KDM-based biological Age (BA) predictors from baseline to follow-up at 52 weeks (Table 1). For the KDM multiple candidate biomarkers based on their relevance in the aging process [7]. Effects of Yoga will also be assessed on several other cardinal mechanistic indicators of aging, markers of inflammaging [IL-6, hsCRP and TNFα], insulin signalling [insulin and IGF-1], renal function [cystatin], senescence [GDF-1], and cardiovascular function [NT-proBNP] [5]. Detailed explanation of secondary markers is given in Table 2.

**Table 1 Tab1:** Primary outcome- biological age

KDM- BA panel	Glycated haemoglobin (HbA1c), Forced expiratory volume in one second (FEV1), Systolic Blood pressure (SBP), Total cholesterol, High sensitive C-reactive protein (hsCRP), Creatinine, Urea nitrogen, Albumin, Alkaline phosphatase (ALP), Cytomegalovirus IgG (CMV IgG), Fasting blood sugar (FBS), Low density lipoprotein – Cholesterol (LDL-c)

*Abbreviations*: *BA* Biological age, *KDM* Klemera–Doubal method based

**Table 2 Tab2:** Secondary outcome panel

Mechanistic Bio markers	IL-6, hs-CRP and Tumour necrosis factor receptor II
	Insulin signaling (insulin and IGF-1)
	Renal function (cystatin)
	Senescence (GDF-15)
	Cardiovascular function (NTproBNP)
Body Composition	Body mass index (BMI)
Aging marker	Telomere length
Strength	Hand grip strength
Locomotion	Gait speed
Balance	Berg balance scale
Cognition	Digit symbol substitution task
Functionality	Activities of daily living

*Abbreviations*: *IL-6* interleukin-6, *hsCRP* high-sensitivity C-reactive protein, *TNF* alpha- Tumour Necrosis Factor alpha, *IGF-1* Insulin-like growth factor 1, *GDF-15* Growth differentiation factor 15, *NTproBNP N*-terminal proBNP, *BNP* Brain natriuretic peptide

### Assessments

The schedule of enrolment, interventions and assessments has been reported according to Standard Protocol Items: Recommendations for Interventional Trials 2013 guidelines in in Table 3. Given the nature of yoga intervention, we cannot do blinding of the participants to the intervention. However, to reduce the potential detection bias, the outcome assessors will be blinded to intervention allocations. An assigned research staff will be performing the assessments and he/she will be blinded to the subject allocation**.** The baseline assessment will be performed before randomisation. The assessment covers basic demographic questionnaire including age and date of birth, sex, marital status, occupation, income, education, co morbidities and medications currently in use will be obtained from each participant. Anthropometric measurements like height, weight, BMI and waist to hip ratio will also be obtained. Alcohol or drug abuse is termed as consumption of 5 plus drinks on one or more occasions during the prior year as an indicator of risky drinking behaviour [33]. Venepuncture will be done post a minimum of 8-h fasting, and blood samples will be collected in EDTA tubes.

**Table 3 Tab3:** Schedule of enrolment, interventions and assessments, according to SPIRIT 2013 guidelines

**Study period**						
**Time points**		Enrolment	Baseline	Intervention	Post intervention	Follow –up
		Week -1	Week 0	Week 1–26	Week 26 + 2	Week 52 + 2
Eligibility screening		x				
Informed consent		x				
Allocation		x				
Intervention				x		
Yoga				x		
Waitlist					x	x
Assessments						
Demographics	Study Proforma		x			
KDM predictors of biological age	Glycated hemoglobin, Forced expiratory volume in one second, Systolic Blood pressure, Total cholesterol, C-reactive protein, Creatinine, Urea nitrogen, Albumin, Alkaline phosphatase, fasting blood sugar, low density lipoprotein- Cholesterol and Cytomegalovirus IgG		x		x	x
Aging marker	Telomere length		x		x	x
Body Composition	Body mass index (BMI)		x		x	x
Mechanistic markers	Inflammation [IL-6, hsCRP, TNF-RII]		x		x	x
	Insulin signaling [Insulin and IGF1]		x		x	x
	Renal function (cystatin)		x		x	x
	Senescence [GDF-15]		x		x	x
	Cardiovascular function [NT proBNP]		x		x	x
Strength	Hand grip strength		x		x	x
Locomotion	Gait speed					
Balance	Berg balance scale		x		x	x
Cognition	Digit symbol substitution task		x		x	x
Functionality	Activities of daily living		x		x	x

### Measuring biological age

Biological Age (BA) will be estimated using the Klemera–Doubal method (KDM) that combines information from multiple clinical biomarkers to quantify aging-related deficits in system integrity [7]. The KDM consists of computation of biological ages from multiple predictors (Glycated haemoglobin (Hba1c) will be measured by using the Beckman Coulter Chemistry Analyser AU480 system according to the manufacturer’s guidelines. A portable spirometer (Schiller spirometer (SP-1A) will be used to test lung function of the participants. Forceful exhalation for 1 s after a maximum inhalation will be set as forced expiratory volume in 1 s (FEV1), Digital BP monitor Omron model HEM-7120 (Omron Healthcare Co. Ltd.) will be used for measurement of Blood pressure at the end of the 5 min of rest as the average of two measurements 60 s apart. Low density lipoprotein-cholesterol (LDL-c), Complete hemogram, Urea nitrogen, Serum creatinine, Total cholesterol, Albumin, Alkaline phosphatase will be assessed by biochemical analyser (Clinical Chemistry Analysers—RX series-Randox), High sensitive C-reactive protein (hsCRP), and Cytomegalovirus IgG (CMV IgG) will be assessed through enzyme linked immunosorbent assay (ELISA- R&D systems) using the linear relationship between predictor and chronological age as classical calibration. We will use the BioAge R package 2 and PhenoAge algorithms first with custom sets of biomarkers, followed by projecting these algorithms onto our datasets [34]. The final product will be KDM-BA in unit of years. To account for the effect of CA, KDM-BA acceleration (KDM-BA acc), defined as the residual resulting from a linear model when regressing KDM-BA on CA will also be calculated.

